**Control group**

The control group consists of parents of preschool children that participate in the study and receive preventive Youth Health Care from one of the 15 YHC-teams that apply 'usual care'. 'Usual care', the control condition in this study, implies care according to the Product Description YHC, i.e. the regular scheme of YHC visits during which general information regarding nutrition, playing and exercise is provided, e.g. through oral information and generic information leaflets, acknowledging the knowledge of the YHC-Overweight Prevention Protocol that states that parents should apply the so-called 'B-BOFT' behaviors to prevent the development of overweight, i.e. breast feeding, daily exercise/outdoor playing, family breakfast daily, few sugar sweetened drinks, minimal TV time (Basistakenpakket Jeugdgezondheidszorg, 2002; Hirasing et al., 2005).

**POWER CONSIDERATIONS AND DETECTABLE DIFFERENCES**

We expect to receive complete data of 1.050 parents/toddlers at follow up at age 36 months old, equally divided over the 2 intervention groups and the control group. We assume equal standard deviations in the intervention groups and the control group, alpha of 0.05 and power of 0.80. We applied a correction factor to account for the cluster design, assuming an average cluster size of 23,3 toddlers (1.050/45) and an intra-class correlation coefficient of 0.10. For this expected sample size and assumptions, we calculated minimal detectable differences between an intervention and the control group at follow-up. We applied standard deviations and proportions/percentages reported in the literature or currently available data from the prior ZonMw projects (# 50-50140-98; # 4010.0033).

Target behaviors at age 36 months old:

Regarding the mean number of the reported minutes of physical activities of the children per day at age 36 months old, the study can detect a difference between intervention/control group of 18 minutes/day (SD=52 min/day). Regarding the mean consumption of sugar-sweetened drinks in glasses per day, a difference of 0.5 glasses/day (SD=1.5 glasses/day) can be detected. Regarding the mean number of minutes of TV viewing per day, a difference of 11 minutes/day can be detected (SD=32 minutes/day).

BMI at age 36 months old:

A difference of 0.44 BMI points between the mean BMI in the intervention group and the mean BMI in the control group at age 36 months can be detected by the study (SD=1.3) (Atkin & Davies, 2000).

Since we will use repeated measures (at age 15 months respectively 24 months in addition to 36 months) as covariates in the analyses, the power will be higher than indicated, which will facilitate the exploration of interaction effects of child gender, social disadvantage, ethnic background, and parental overweight status.

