The 'BOFT+' intervention has - as primary starting point - a focus on child rearing issues that are relevant for the development of behaviors related to overweight. By doing so it aims at implementing healthy life-style habits continuously, from early age on (from birth on) during guidance offered to parents by YHC in the whole preschool period. An authoritative parenting style means high levels of effective parenting, not many inter-parental conflicts en high parental self-efficacy. A healthy lifestyle can be reached by healthy eating, physical activity and the use of positive parenting. In the current study the effect of the intervention up to (and including) age 24 months old will be evaluated with a final follow-up measure at age 36 months.

The strategy of the 'BOFT+' intervention is based on results of a previous study on determinants of behavior that is related to overweight in young children (Boere-Boonekamp 2005; ZonMw Grant # 50-50140-98). In this intervention the education and counseling will not only focus on eating habits and exercise, but also on childrearing issues, by using elements of the learning theory and enlarging parental sensitivity together with high expectations concerning the possibility of self-control of the child (the so called authoritative parenting style. YHC nurses will apply the new approach during each YHC-contact with parent(s) in the preschool period. Examples of the techniques that will be used are: modeling, stimulus control, operant conditioning such as intermittent confirmation.

(b) The 'Healthy toddler' intervention

The 'Healthy toddler' intervention has - as primary starting point - a direct focus on four behaviors related to overweight as defined in the YHC-Overweight-prevention-protocol that start to be of relevance in young toddlers: daily exercise/outdoor playing, family breakfast daily, few sugar sweetened drinks, minimal TV time (so-called 'BOFT' behaviors). Child rearing issues related to these behaviors are addressed as well in the 'Healthy toddler' intervention.

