**TIME SCHEDULE IN MONTHS**

The schedule below is provided in months from the start of the project, which is scheduled at July 1, 2008.

0-6: Recruiting 45 YHC-centers, preparing procedures/measures/protocols, and (start of) training of YHC-professionals regarding 'BOFT+' (15 YHC-teams) and the 'Healthy toddler' (15 YHC-teams) interventions.

6-18: During a year 3.000 parents of newborns will be provided information about the study and will be asked informed consent by 60 YHC-teams (expected participation rate at least 50%).

6-19: After recruitment of 1.500 parents/newborns, baseline measurements (T0 at child age 1 month) will be performed in the 3 study arms.

6-19: In the 'BOFT+' study arm (15 YHC-teams) the 'BOFT+' intervention will be started regarding 500 parents/newborns at child age 1 month.

12-24: Measurements at child age 6 months in 1.500 parents/infants (T1).

21-33: Measurements at child age of 15 months in 1.500 parents/infants (T2).

23-37: In the 'Healthy toddler' study arm (15 YHC-teams) the first part of the 'Healthy toddler' intervention will be applied to 500 parents/toddlers at child age of circa 18 months.

29-43: In the 'Healthy toddler' study arm (15 YHC-teams) the second part of the 'Healthy toddler' intervention will be applied to 500 parents/toddlers at child age of circa 24 months.

30-42: In the 'BOFT+' study arm (15 YHC-teams) the last scheduled contact moment between YHC-team and parents regarding the 'BOFT+' interventions will take place regarding 500 parents/toddlers at child age 24 months.

42-54: Measurements at child age of 36 months in 1.500 parents/infants (T3).

6-55: Data entry, and data cleaning.

18-60: Analyses, dissemination of the results.

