#### T1. DATA COLLECTION AT CHILD AGE 6 MONTHS

The following data will be collected at child age 6 months (T1).

- Weight and length of the child (from YHC-file);
- History of breast/bottle feeding; supplemental feeding/introduction of solid food; family eating practices;
- Health and well-being of the parent: SF-12 (Gandek et al., 1998);
- In case of siblings in the family: Parent Problem Checklist (PPC) (Dadds et al., 1991);
- Health and well-being of the child: subscales of the Infant Toddler Quality of Life questionnaire (ITQOL) (Raaijmakers et al., 2007).

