### **TO BE REGISTERED IN YHC-CENTERS (24 MONTHS)**

Additionally will be recorded at child age 24 months:

Weight and length of the child, and waist circumference.

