**Co-variables:**

- \*\* Pregnancy characteristics of the child, birth weight and length, lowest weight.
- \*\* Parents' and siblings' height and weight using self report and medical files. Self-report of adult height and weight has proven to be sufficiently accurate for epidemiological research (McAdams et al., 2007).
- \*\* Parents' health and well-being (SF-12; Parent Problem Checklist).
- \*\* General demographics, including educational level and ethnicity of the parents.
- \*\* Non response measures, including general demographics and reasons for non-participation

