## 7. STATISTICAL ANALYSIS

### **Intervention effect:**

To assess the intervention effect, multilevel analyses will be applied to allow for dependency between the individual measurements within the randomized YHC-teams (Campbell et al., 2004). The multilevel approach is also appropriate for the analyses regarding longitudinal data in the study. Multilevel linear regression analyses will be conducted for the continuous outcome variables with group (intervention or control) as independent variable and baseline values and potential confounders as covariates. Multilevel logistic regression will be performed in case of dichotomous outcome variables.

Additionally, effect modification by gender, parental educational level, ethnicity, and parental overweight status will be conducted by introducing an interaction term into the regression analyses. If this interaction term reaches statistical significance, stratified analyses will be carried out.

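### Adjusting 36-month outcomes for 15- and 24-month values conditions on measurements taken after BOFT+ has started (and, at 24 months, after Healthy toddler has started), so part of the effect is removed and the claimed power gain is not assured

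*Protocol*

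**What the plan says.** Section 4 (Power considerations and detectable differences) first gives the differences detectable at 36 months with no covariate gain. It then closes with "Since we will use repeated measures (at age 15 months respectively 24 months in addition to 36 months) as covariates in the analyses" and concludes that true power will exceed the calculated level, which is to help the exploration of interactions. Section 7 (Intervention effect) describes multilevel regression "with group (intervention or control) as independent variable and baseline values and potential confounders as covariates"; it does not mention 15 or 24 months.

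The timing is as follows.

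- **BOFT+.** The time schedule in Section 3 states that the "intervention will be started regarding 500 parents/newborns at child age 1 month". Section 3 adds that "the effect of the intervention up to (and including) age 24 months old will be evaluated with a final follow-up measure at age 36 months". Figure 2 in Section 5 lists contacts from about 3 to about 14 months.
- **Healthy toddler.** Packages are given at about 18 and 24 months, each preceded by the E-health module about a month before the visit. Section 5 lets the age vary by region, down to 14 months.
- **Measurements.** T0 (1 month) records pregnancy, newborn, parent and sibling data, and none of the four target behaviors. The behaviors are collected at T2 (15 months) and T3 (36 months). T2 weight and length come from the file at 14 months. The 24-month record is "Weight and length of the child, and waist circumference".

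Section 2 asks for the effects, at about 36 months, of BOFT+ given from birth and of Healthy toddler given from toddler age. Mediation is a separate analysis in Section 7.

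**The concern.** The study question concerns the whole effect of each intervention at 36 months. A covariate measured after an intervention has started may already carry some of that effect. Regression then credits that part to the covariate, and the arm coefficient estimates only what was added later.

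For BOFT+ this touches the behaviors (15-month covariate) and body size (T2 or 24-month covariate). For Healthy toddler it touches body size when the 24-month value is used. A null result on these contrasts could not be told apart from over-adjustment.

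The analysis section does not settle the matter. It calls for baseline values, but T0 holds no behavior values, so an outcome-specific baseline for a behavior could only be T2. For BOFT+, T2 comes more than a year after the start.

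**Working it through.** **Inputs from the protocol.** 350 children per arm (1,050 in three equal arms), average cluster size 1,050/45 = 23.33, intra-class correlation 0.10, alpha 0.05, power 0.80, BMI SD 1.3 and TV viewing SD 32 min/day.

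**The plan's own figures.** The design effect is 1 + (23.33 − 1) × 0.10 = 3.233. The effective size is 350/3.233 = 108.2 per arm. The standard error is SD × sqrt(2/108.2) = 0.136 SD.

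- One-sided alpha: (1.645 + 0.842) × 0.136 × 1.3 = 0.439 for BMI and 10.8 min for TV. These match the stated 0.44 and 11.
- Two-sided alpha: 0.495 and 12.2 min. At a true BMI difference of 0.44, two-sided power is 0.70.

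The plan does not state sidedness; that is a separate matter. The powers below are two-sided. The break-even result further down does not depend on this choice.

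**Effect of adjustment.** Let D be the true 36-month difference, rho the within-arm correlation between the covariate and the 36-month value, and f the share of D already present when the covariate is measured. With equal SDs the regression slope is rho, so

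- adjusted effect = D − rho × fD = D × (1 − rho × f);
- standard error = unadjusted standard error × sqrt(1 − rho²).

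The second line treats the correlation as equal between and within teams, and ignores a small extra variance from imbalance of the covariate between arms.

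**Results.** The documents give neither rho nor f, so both are assumed over a range. For BMI with D = 0.44 and unadjusted power 0.70, each cell shows the adjusted effect and its power:

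| rho | f = 0 | f = 0.5 | f = 1 |
|---|---|---|---|
| 0.3 | 0.44; 0.74 | 0.37; 0.60 | 0.31; 0.45 |
| 0.5 | 0.44; 0.82 | 0.33; 0.58 | 0.22; 0.30 |
| 0.7 | 0.44; 0.94 | 0.29; 0.62 | 0.13; 0.18 |

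One cell in full, rho = 0.5 and f = 0.5: effect 0.44 × 0.75 = 0.33; standard error 0.136 × 1.3 × sqrt(0.75) = 0.153; power = Phi(0.33/0.153 − 1.96), about 0.58.

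The same pattern holds for a behavior. A true TV difference of 11 min/day at rho = 0.5 becomes 8.25 min at f = 0.5 and 5.5 min at f = 1.

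A simulation with 15 teams per arm, 23 children per team, intra-class correlation 0.10 and 400 runs per setting gave mean adjusted BMI effects of 0.332 (rho 0.5, f 0.5), 0.228 (rho 0.5, f 1) and 0.124 (rho 0.7, f 1). These agree with the formula.

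**Break-even.** Adjustment lowers power once 1 − rho × f < sqrt(1 − rho²), that is, once f > (1 − sqrt(1 − rho²))/rho:

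- rho 0.3: (1 − 0.954)/0.3 = 0.15
- rho 0.5: (1 − 0.866)/0.5 = 0.27
- rho 0.7: (1 − 0.714)/0.7 = 0.41
- rho 0.8: (1 − 0.600)/0.8 = 0.50

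**The case against.** The best defence is that the sentence is a loose aside. It counts 36 months, the outcome itself, among the measures, which fits a repeated-measures model. Section 7 names only baseline values and says that the multilevel approach suits longitudinal data. The stated detectable differences do not rely on the sentence, and the extra power is invoked only for exploring interactions. All of this is fair, and it means that Section 7 cannot be cited as prescribing the adjustment. But Section 4 does say that the measures enter as covariates. If a repeated-outcomes model is meant, the sentence is still wrong and needs correcting.

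A reader might infer more than the documents support:

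- **That every contrast is affected.** Healthy toddler versus control on the four behaviors normally is not. Its 15-month value precedes the first package, except where that is applied early, and no behaviors are recorded at 24 months.
- **That a 24-month power gain is claimed for behaviors that are not measured then.** The word *respectively* plausibly pairs 15 months with the behaviors and 24 months with BMI. On that reading no such claim is made.
- **That post-start parental measures are adjusted for.** Section 6 lists "Parents' health and well-being (SF-12; Parent Problem Checklist" among the co-variables, and at 6 months the checklist is collected only "In case of siblings in the family: Parent Problem Checklist (PPC". But that list is an inventory, which also contains reasons for non-participation. Nothing says that these scales enter the effect model.
- **That the power claim is simply reversed.** That depends on f. For Healthy toddler only one package normally precedes the 24-month visit, so f = 1 there would be extreme.

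**Conclusion.** The point holds for BOFT+ versus control on behaviors and body size, and for Healthy toddler versus control on body size adjusted for the 24-month value. It extends to Healthy toddler with T2 only where the package is applied before T2 is completed.

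For rho 0.3 to 0.7, adjustment keeps 85% to 65% of the effect at f = 0.5 and 70% to 30% at f = 1. The promised power gain is therefore not assured, and it turns into a loss beyond the break-even shares shown above. For BOFT+ such shares are plausible, because every contact listed in Figure 2 precedes the 15-month questionnaire.

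The size rests on assumed values of rho and f, equal SDs at the two ages, and an effect in the same direction already present at the earlier visit. If no effect exists by then (f = 0), nothing is lost and power does rise. The documents cannot show which case applies, so the choice of covariates should not depend on it.

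**What to change.** Align Section 4 with Section 7 and state the following.

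1. The total effect of BOFT+ versus control is estimated adjusting only for T0 variables, such as birth weight and length, sex, parental education, ethnicity and parental BMI.
2. T2 may be a covariate only for Healthy toddler versus control, and only when it was completed before the first Healthy toddler element, which is the E-health module ahead of the visit. This needs the two contrasts to be modelled separately, with both dates on file.
3. The 15-month values (for BOFT+) and the 24-month body-size values (for both arms) are repeated outcomes in the multilevel model, or are kept for the separate mediation analysis. They are not covariates for the total effect.
4. The sentence on higher power is limited to Healthy toddler with a T2 value obtained before the intervention.

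The cost is a change of wording that uses measurements already planned. The claimed power gain is lost for BOFT+, and for body size in Healthy toddler insofar as it came from the 24-month value. The stated detectable differences are unchanged, since they assume no covariate gain.

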## **5. DESCRIPTION OF THE INTERVENTIONS**

In addition to the descriptions above, in this paragraph we describe the theoretical framework of (a) the 'BOFT+'- and (b) The 'Healthy toddler' interventions that will be evaluated in this study. The content of both interventions will be described in the text, as well as in an appendix with a schematic overview of both 'BOFT+'- and the 'Healthy toddler' intervention.

### **A. THE 'BOFT+' INTERVENTION**

The 'BOFT+' intervention is intended to promote the key behaviors for the prevention of overweight in children as defined in the YHC-Overweight Prevention Protocol from early age on: 1. Promotion of breastfeeding, 2. Promotion of outside exercise, activity and play, 3. Promotion of having breakfast, 4. Discouragement of soft drinks, and 5. Discouragement of television viewing. Promotion of breastfeeding has a specific context, is mainly limited to the first year of life, and is not the main focus of the 'BOFT+' intervention. Behaviors 2-5 relate to child rearing issues that are the primary focus of 'BOFT+'; these child-rearing issues are introduced from birth on in the 'BOFT+' intervention.

The 'BOFT+' intervention includes targeted education that anticipates on common problems and explains the basics of stimulus control and classic conditioning in order to enable parents to create the conditions that stimulate desired behavior in the child. Concrete examples and advice on the subject of exercise and eating habits, derived from our previous study that may prevent weight problems in young families will be incorporated (Boere-Boonekamp 2005).

***Theoretical framework of the 'BOFT+' intervention***

The 'BOFT+' intervention focuses on parenting styles used within the families. It is essential that health care workers in the YHC centers (well-baby clinics) are educated about social learning principles, the different parenting styles and the associated risks. Furthermore, they have to be able to disseminate this knowledge, know how to coach parents in achieving competent parenting. Social learning principles can be dichotomized into classic and operant conditioning.

Specific behavior is caused by antecedent factors. One tries to intervene before the unwanted behavior occurs, and to create conditions suitable for positive behavior. Parents learn that it is important to set clear boundaries, have unambiguous rules. They receive suggestions to help structure time and space, how to introduce ground rules, and how to state these rules clearly, consistently. Parents should collaborate as a team in defining the rules and applying them consistently. By controlling the stimuli in this manner, disruptive behavior can be avoided (Bosch 1997). These principles are the basis of the learning theory.

Three targets of the BOFT+ approach are:

- a. Enlarge parenting skills;
- b. Optimize nutrition;
- c. Optimize physical activity.

Ad a. Enlarging parenting skills is operationalized as:

- increase children's self esteem by spending time with the child, talk and show affection to the child. Regularly interact with a child while it is behaving positive, and talk with children about their activities, cuddle, touch and hold the child (bodycontact).
- encourage healthy behaviors: reinforce positive behavior by praising the specific behavior
- give positive attention: offer non-verbal attention (smiling, touching)
- offer attractive activities: play material etc. (age and development phase related)
- parent is positive example (modeling);
- reinforce spontaneous learning moments
- reinforce learning by experience, instruction

Stimulus control

Basic rules and regulations (age en development phase related)

Direct intervention when child is misbehaving

Clear instructions in a quiet way

Operant conditioning

Misbehavior will be related to direct consequence

Time out

Ad b. Optimize nutrition is operationalized as:

- establishing eating routine (0-9 months regularity and stimulus reduction (Sleuwen van, 2006); > 6 months specific times for meals and snacks (stimulus control);
- prevention of introduction of extra foods (commercial snack foods, take aways, sugar drinks)
- provision of healthy alternatives

ad c. Optimize physical activity is operationalized as:

- prevention of sedentary activities (TV etc.)
- increase physical activity (daily walk, play-pen, play outside etc.)

These three intervention targets are related to the child's body size, food intake, child behavior and parenting. They are described in detail by age (and developmental phase) in the Annex and in the report: "Ingredients of an intervention" based on the determinant study conducted by Boere-Boonekamp e.a. (2005; ZonMw Grant: # 50-50140-98).

Parents will enlarge their parenting skills by increasing children's self-esteem, encouraging healthy behavior by setting a good example and using praise and reward in the correct way and by managing problem behaviors by setting ground rules, clear instructions and the use of consistent consequences (Bakker & Husmann 1994; West 2007).

The 'BOFT+' intervention is relatively simple and easily communicated by YHC workers to parents. In this intervention behavioral goals are set out: these goals will be partially derived from our earlier study on behavior in young families that puts children at risk of weight problems (Boere-Boonekamp 2005). The goals cover specific issues of eating behavior, exercise and activities. The intervention targets parenting skills in the context of everyday, naturally occurring examples. Specific anticipating parenting education will be given during the standard YHC (well-baby) visits. The principles of stimulus control, modeling and operant conditioning will be taught (ZonMw project # 50-50140-98).

Please refer to the scheme (below, Figure 2) of the specific elements of the 'BOFT+' intervention according to child age.

Figure 2. Flowchart of the 'BOFT+' intervention.

| Activity by YHC professional                                                                                                                               | Theme                                                                                                                                                                                                                                    | Age of the child |
|------------------------------------------------------------------------------------------------------------------------------------------------------------|------------------------------------------------------------------------------------------------------------------------------------------------------------------------------------------------------------------------------------------|------------------|
|                                                                                                                                                            |                                                                                                                                                                                                                                          |                  |
| Targeted education anticipating on common problems and explaining the basics of stimulus control, classical conditioning, modelling, operant conditioning. | 
 
- Breastfeeding, bottle feeding (amount, extra powder, self-regulation);
 
- Taste development;
 
- Use of playpen and television.
 
- Crying and sleeping rhythm
 
 | ± 3 months       |
|                                                                                                                                                            | Reminder of the above themes.                                                                                                                                                                                                            | ± 4 months       |
|                                                                                                                                                            | Reminder of the above themes.                                                                                                                                                                                                            | ± 6 months       |
| Targeted education anticipating on common problems and explaining the basics of stimulus control, classical conditioning, modelling, operant conditioning. | 
 
- Introduction of sweetened drinks;
 
- Number of eating moments;
 
- Crying and sleeping rhythm
 
- Television viewing.
 
                                          | ± 7,5 months     |
|                                                                                                                                                            | Reminder of the above themes.                                                                                                                                                                                                            | ± 9 months       |
| Targeted education anticipating on common problems and explaining the basics of stimulus control, classical conditioning, modelling, operant conditioning. | 
 
- How to eat with a child at the dinner table;
 
- Going outdoor for a walk, playing outdoors;
 
- Sleeping rhythm;
 
- Television viewing.
 
                       | ±11 months       |
| Targeted education anticipating on common problems and explaining the basics of stimulus control, classical conditioning, modelling, operant conditioning. | 
 
- Television viewing
 
                                                                                                                                                                   | ± 14 months      |

